#### Cost-effectiveness

At 1-year follow-up, a cost-effectiveness analysis will be performed from a healthcare system perspective, based on recorded therapist time, as well as from a societal perspective. The incremental cost-effectiveness ratio will be estimated at post-treatment and at follow-up. We will also use the TIC-P to collect economic cost data,^34^ together with the EQ-5D.^35^ The costs will be assessed in Swedish krona and converted into US dollar using 2023 as the reference year. The costs of the self-guided and therapist-guided treatments will be modelled as a function of therapist time using the same healthcare index to determine tariffs for licensed psychologists. According to our hypothesis, there should be a significant difference in treatment costs but there should not be any significant difference in societal costs. We will calculate quality-adjusted life-years using the area under the curve approach,^37^ use regression analyses to analyse costs^38^ and use non-parametric bootstrapping with 5000 iterations, where differences in costs and outcomes will be paired. The incremental cost-effectiveness ratio will be used as a cost-effectiveness estimate.^39^

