#### Hypotheses

##### Primary hypothesis

Digital self-care will be non-inferior to ICBT, according to the predefined non-inferiority margin of three points, as measured by the primary outcome (POEM).

##### Secondary hypothesis 1

Digital self-care will be associated with significantly less staff costs than ICBT, in the form of time spent in hours by a licensed psychologist.

##### Secondary hypothesis 2

Digital self-care will be cost-effective compared with ICBT, assessed at 1-year follow-up.

##### Secondary hypothesis 3

Effects on the outcome will be mediated by the amount of time spent by participants on main treatment components.

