
#### Digital self-care

As with guided care, the aim of CBT for AD is to target behavioural and emotional processes, to improve AD symptoms and increase quality of life. The material is similar to guided care but shortened. Likewise, participants, read information and perform exercises in their everyday life. As with guided care, the main treatment components are mindfulness and exposure with response prevention, with a specific focus on itch. Participants will be able to practice mindfulness with the help of instructions and examples. Because it may be challenging to construct relevant exposure exercises without the help of a therapist, participants will receive detailed instructions and guidance, and get to choose exposure exercises from a long list of examples. They will also be free to create their own relevant exposure situations within the intervention. Digital self-care consists of eight modules. The only active interventions, mindfulness and exposure are introduced weeks 1 and 2, respectively. From weeks 3 to 7, no new interventions are introduced and participants are advised to continue practising the interventions, but there is a new theme of education each week, to act as inspiration for exercises. The last 4 weeks, the participant is merely advised to continue practice. There is no therapist, but the study coordinator monitors the process and may contact inactive participants. Participants will access the same digital platform as the guided condition. Participants work entirely at their own pace. Modules will be unlocked automatically if 1 week has passed, and all material in the previous module has been read. Participants will report if they have done their assignments, but there is no control if they do as they report.

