#### Therapists

Only the guided group will have therapist contact. The self-guided group will be managed by the study coordinator. The therapists are licensed psychologists specialised in CBT. All therapists have experience in working with somatic conditions and in a text-based format. All therapists will participate in an introductory workshop before treating in the study. The project coordinator will supervise the therapists regularly and on-demand.

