##### Secondary outcome measures

Demographical data will be collected on screening. Peak pruritus Numerical Rating Scale^27^ is used to measure itching sensations; Perceived Stress Scale^28^ is used to measure general experience of stress; Patient Health Questionnaire-9^29^ is used to measure depressive symptoms; Dermatological Life Quality Index^30^ is used to measure AD-specific quality of life; Insomnia Severity Index^31^ is used to measure severity of sleep problems and possible insomnia; Client Satisfaction Questionnaire-8^32^ is used to measure how satisfied participants are with the intervention. We will also ask participants to report if they experience adverse events associated with the treatment (AE). In addition to this, we will use the Credibility/Expectancy Scale^33^ to measure credibility. At the end of the intervention, the participants will be asked to estimate the Time spent in the Exercises (ToE). Euro-QOL Five Dimensions (EQ-5D)^34^ will be used to assess quality of life from a health economics perspective. Treatment Inventory of Costs in Psychiatric Patients (TIC-P)^35^ will be used to assess healthcare costs. Participant will also rate their user experience of the interventions with the System Usability Scale.^36^ Resource use is measured by the time in minutes the clinician spends on the different tasks associated with administering the intervention, doing interviews, and giving support, or Time spent on Treating. Therapists will register their time spent throughout the intervention, and not at a specific measurement point.

Outcomes at all scales will be compared with available published results regarding other internet-based interventions for each scale.

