#### Resource utilisation

At the primary endpoint, resource utilisation will be preliminary assessed by measuring therapist time for each treatment condition and compared with a typical salary for a clinical psychologist employed in Stockholm, Sweden.

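### Both arms are costed on therapist time, but self-care is run by a coordinator whose time nobody is told to log, so the staff-cost difference can be biased in either direction

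*Protocol article*

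**What the plan says.** The protocol describes the staff input to be costed in four places, with three different terms.

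- Secondary hypothesis 1 predicts lower staff cost for self-care, "in the form of time spent in hours by a licensed psychologist".
- Secondary outcome measures defines resource use as minutes of the clinician, covering administration of the intervention, interviews and support. The only logging instruction follows there: "Therapists will register their time spent throughout the intervention".
- Resource utilisation plans an assessment at the primary endpoint by "measuring therapist time for each treatment condition".
- Cost-effectiveness says: "The costs of the self-guided and therapist-guided treatments will be modelled as a function of therapist time". The rate applied to that time is the licensed-psychologist tariff in both arms. The section describes the first analysis as "from a healthcare system perspective, based on recorded therapist time", with a societal perspective alongside.

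On who does the work, the Therapists section says: "Only the guided group will have therapist contact. The self-guided group will be managed by the study coordinator". The Digital self-care section says: "There is no therapist, but the study coordinator monitors the process and may contact inactive participants". The Therapists section adds that the project coordinator supervises the guided-arm therapists, both regularly and on request. The section on differences between conditions gives each arm two contacts with a clinician.

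TIC-P is described under Secondary outcome measures as the instrument for healthcare costs. Table 1 schedules it at pre, mid, post, 6 months and 12 months.

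**The concern.** The cost driver is a staff category that the self-care arm is said not to have, and the person who does run that arm appears neither in the cost model nor in the logging instruction. One task shows the asymmetry. Following up inactive participants is done by the therapist in guided care, where it is logged and costed. In self-care the coordinator does it, and nothing says that it is logged.

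The same role also supervises therapists, which is work that only guided care generates. That time is not said to be logged either.

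Two results depend on this: the staff-cost comparison (secondary hypothesis 1) and the intervention-cost component of the cost-effectiveness analysis (secondary hypothesis 2). A health service deciding whether to offer the unguided version needs to know what it costs to run, including the person who keeps it running.

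A related gap concerns the healthcare-system perspective. Participants who worsen are referred to their ordinary specialist or primary care (Safety considerations). If such visits differ by arm, they are health-system costs that therapist time cannot show. The trial collects them with TIC-P, but the Cost-effectiveness section does not say that they enter this perspective.

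**Working it through.** The protocol gives no minutes or costs per arm, so there is no figure of its own to reproduce. The check has two parts.

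**1. Which staff time is counted on a literal reading**

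| Task | Arm | Done by | Told to log time? |
|---|---|---|---|
| Messages, feedback, follow-up of inactive participants | Guided | Therapist | Yes |
| Supervision of therapists | Guided | Coordinator | Not stated |
| Monitoring, follow-up of inactive participants | Self-care | Coordinator | Not stated |
| Two clinician contacts | Both | Clinician | Only if the clinician counts as a therapist |

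The protocol uses both study coordinator and project coordinator. I take them as one role. If they are two people, the gap is the same, because neither is told to log time.

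**2. What omission could do to the estimated saving**

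Inputs:
- Guided support: about 15 minutes per patient and week, from the background section on internet-delivered CBT. This is a general figure, not a trial input.
- Duration: 12 weeks, so 15 × 12 = 180 minutes per guided participant.
- c = coordinator minutes per self-care participant. Not given; assumed 12 to 60 (1 to 5 minutes a week).
- s = supervision minutes per guided participant. Not given; varied from 0 upwards.
- The two clinician contacts per arm are assumed equal and cancel.
- All minutes are valued alike. A different coordinator tariff would scale c and s in money terms.

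Formulas:
- Recorded saving, coordinator time omitted in both arms = 180
- Full saving = 180 + s − c
- Relative error = (180 − full saving) / full saving

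| c | s | Full saving (min) | Error in recorded saving |
|---|---|---|---|
| 12 | 0 | 168 | 12/168 = +7% |
| 24 | 0 | 156 | 24/156 = +15% |
| 36 | 0 | 144 | 36/144 = +25% |
| 60 | 0 | 120 | 60/120 = +50% |
| 24 | 24 | 180 | 0% |
| 12 | 24 | 192 | −12/192 = −6% |
| 12 | 36 | 204 | −24/204 = −12% |

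The sign depends only on whether c exceeds s, and the protocol gives neither.

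**The case against.** The strongest reply is that therapist time in the two cost sections is shorthand for the broader measure under Secondary outcome measures, which already covers administration, interviews and support. Time is to be measured in each condition, which presupposes some self-care time. The Guided care section speaks of the coordinator guiding other therapists, which suggests that the coordinator is also a therapist and so, by the Therapists section, a licensed psychologist. On that reading coordinator minutes fit all three terms. The self-care workload may also be light, since modules unlock automatically and the weekly emails are automated.

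This rules out some stronger readings. A reader might infer that self-care is assigned zero therapist time, so that secondary hypothesis 1 is true by definition. The documents do not support that: self-care has two clinician contacts, and interviews count as resource use. A reader might also infer that the saving is certainly overstated. That does not follow, because uncounted supervision pulls the other way.

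The reply does not close the gap. It needs the broad definition to override the narrower term in both sections that specify the analyses, and it needs the coordinator to count as a therapist in an arm described as having none. Nor does it supply a logging instruction for the coordinator.

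On TIC-P, the data are collected and are mentioned in the Cost-effectiveness section, so they are not lost to the evaluation. Assigning components to perspectives could be left to a fuller plan. But the article does not stay silent here: it states a basis for the healthcare perspective, and that basis is therapist time. Finally, lower psychologist input is the purpose of self-care, so expecting a saving is no error; the issue is whether its size will be measured correctly.

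**Conclusion.** The concern holds as a defect in how the cost measure is fixed, not as a demonstrated bias in one direction. Followed literally, the plan leaves coordinator time out of both arms. Leaving out monitoring and contact understates the cost of self-care; leaving out supervision understates the cost of guided care.

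The net effect cannot be derived from the document. The illustration runs from a 50% overstatement of the saving, through zero, to an understatement. It rests on a background figure of 15 minutes a week, assumed coordinator and supervision minutes, equal clinician contacts and equal tariffs. It should not be quoted as an estimate for this trial.

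The healthcare-system perspective, as worded, is based on therapist time and is not assigned the healthcare use that TIC-P collects. The consequences are confined to secondary hypotheses 1 and 2. The POEM non-inferiority analysis is untouched.

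**What to change.** Use one measure in Secondary hypothesis 1, Secondary outcome measures, Resource utilisation and Cost-effectiveness: all delivery-staff minutes per participant, by arm. It should include therapist time, coordinator monitoring and contact, clinician interviews, and supervision allocated to guided care. Exclude tasks done only for research. Cost each component at the tariff for the staff who do it.

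State that the coordinator logs time by arm, in the same way as the therapists. Define the healthcare-system perspective as this intervention cost plus the healthcare use from TIC-P.

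The cost is a small logging burden and a few sentences of text. The first participant was included on 29 November 2022, so coordinator time for early cohorts will have to be estimated. That estimate should be labelled as such and varied in a sensitivity analysis.

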#### Power calculation

Based on data from Hedman-Lagerlöf *et al*
17 and Kern *et al,*
19 we expect an in-group effect of about d=0.85 for both interventions. A consultant statistician performed a power calculation. The required sample size was computed based on boot-strapped (5000 simulations) reruns of weekly measured data obtained in the therapist-guided RCT.^17^ The results indicated that a sample size of 174 would be required for 90% power, α=0.05, given a non-inferiority margin of 3 points on the POEM scale and accounting for 10% missing data.

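### The ICER is named as the cost-effectiveness estimate in a trial that expects about equal effects, so its denominator is expected near zero; a non-significant societal cost difference should also not be read as equal costs

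*Protocol article*

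**What the plan says.** Secondary hypothesis 2 (protocol article, Hypotheses) reads: "Digital self-care will be cost-effective compared with ICBT, assessed at 1-year follow-up". The Cost-effectiveness section names one summary measure: "The incremental cost-effectiveness ratio will be used as a cost-effectiveness estimate". On timing it says: "The incremental cost-effectiveness ratio will be estimated at post-treatment and at follow-up". It plans both a healthcare and a societal perspective, with QALYs by area under the curve. For uncertainty the authors will "use non-parametric bootstrapping with 5000 iterations, where differences in costs and outcomes will be paired". On costs the stated expectation is that "there should be a significant difference in treatment costs but there should not be any significant difference in societal costs".

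The Power calculation section says: "we expect an in-group effect of about d=0.85 for both interventions". The primary hypothesis is non-inferiority.

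**The concern.** An ICER divides the cost difference by the effect difference. It reads well when the effect difference is clearly away from zero. Here the trial's premise is similar effect at lower cost, so the denominator is expected near zero. Three consequences follow.

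- The ratio can take either sign while the saving stays the same. Negative means cheaper and slightly better; positive means cheaper and slightly worse.
- A positive value in the cheaper-and-worse quadrant is a saving per QALY given up. There a larger value favours self-care, the reverse of the usual threshold rule.
- From the societal perspective the cost difference is also expected near zero. A negative ICER then covers both cheaper-and-better and dearer-and-worse, and a positive one covers the other two quadrants.

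The societal cost wording raises a second issue. Costs vary widely between patients, and a trial sized on POEM may miss a cost difference large enough to cancel the saving in therapist time. If a non-significant result is taken to confirm the expectation, lack of information is reported as agreement.

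**Working it through.** **The plan's own figures.** The article gives no sample size, SD or unit cost for the health-economic analysis, so there is no figure of that kind to reproduce. It gives 174 participants, 1:1 allocation and 10% missing data: 174/2 = 87 per arm, and 87 × 0.9 = 78.3, taken as 78 analysed.

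**Other inputs.**
- From the article (Background, on internet-delivered CBT): about 15 minutes of clinician time per patient and week. Over 12 weeks, 15 × 12 = 180 minutes = 3 hours.
- Assumed: USD 60 per hour, so a saving of 3 × 60 = 180, with standard error 15; QALY SD 0.10 (range 0.05 to 0.20); societal cost SD USD 5,000; cost and effect differences independent.

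**Step 1: sign of the ICER.** Let ΔC be the cost difference and ΔE the QALY difference, self-care minus guided care. With ΔC below zero, the ICER is positive exactly when ΔE is negative. With ΔE normal, mean δ and SE = SD × √(2/n), this has probability Φ(−δ/SE).
- δ = 0: Φ(0) = 0.50, whatever the SD.
- δ = 0.01 QALY in favour of self-care, n = 78: SD 0.10 gives SE 0.0160 and 0.27; SD 0.15 gives SE 0.0240 and 0.34; SD 0.20 gives SE 0.0320 and 0.38.

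**Step 2: spread of the ICER.** Take ΔC as −180 and δ = 0. The central 95% range is ±L, where P(|ΔE| < 180/L) = 0.05. So 180/L = 0.0627 × SE, and L = 180/(0.0627 × SE).
- 87 per arm, SD 0.10: SE 0.0152, L about 189,000 USD per QALY. A simulation of 5,000 draws gave −207,000 to +203,000, the same order.
- 78 per arm, SD 0.10: SE 0.0160, L about 179,000.
- 78 per arm, SD 0.05: L about 359,000. SD 0.20: L about 90,000.

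Noisier QALY data give a narrower range, so the spread of this ratio does not measure precision.

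**Step 3: societal costs.** SE = 5,000 × √(2/78) = 801.
- 95% half-width: 1.96 × 801 = about 1,570.
- Difference detectable with 80% power: 2.8 × 801 = about 2,240.
- Probability of a non-significant result, Φ(1.96 − Δ/801): 0.91 at a true difference of 500, 0.76 at 1,000, 0.53 at 1,500, 0.20 at 2,240.

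Without a currency assumption, for a true difference of 20% of mean cost, the probability of non-significance is 0.76 if the SD equals the mean and 0.91 if the SD is twice the mean. The detectable differences are 45% and 90% of mean cost.

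**Step 4: net monetary benefit on the same inputs.** NMB = λ × ΔE − ΔC, with λ the willingness to pay per QALY. It is linear in both differences, so it is defined at ΔE = 0, where its expected value is 180 for every λ. Its standard error is √(λ² × 0.0160² + 15²). The 95% half-width equals 180 when λ = √((180/1.96)² − 15²)/0.0160 = 90.6/0.0160, about 5,700 USD per QALY. Above that value the expected interval includes zero. Net benefit therefore makes the result readable; it does not make it precise.

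**The case against.** The strongest reply is that the article commits to less than a critic may read into it. Much of this stands.

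- A reader might infer that hypothesis 2 will be accepted if the societal cost difference is non-significant. The text does not say so. The sentence is a prediction, and no passage declares costs equal when p exceeds 0.05. What remains is that this is the only testable form given for societal costs, with no margin, whereas the primary outcome has one.
- A reader might go further and say the prediction would come true almost whatever the true difference. Step 3 refutes that: at about 2,240 it would fail in 80% of trials.
- A reader might conclude that hypothesis 2 has no interpretable estimate. The paired bootstrap yields the joint distribution of cost and effect differences, which separates the quadrants. From the healthcare perspective the sign of the cost difference is expected to be known, so the quadrant can be read. But the text links the bootstrap to no decision measure, and resampling does not stabilise a ratio whose denominator straddles zero.
- A reader might assume that percentiles of the bootstrapped ratio will be reported. The article does not plan this. Step 2 describes how the ratio behaves, not a planned interval.
- Thresholds and acceptability curves are often left to a fuller plan that is not shown. Their absence is not the point; the point is the measure the article does name.

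The illustration has limits too. Equal QALYs is an inference from equal expected within-group effects. The 3 hours gives self-care no offsetting staff time, although its coordinator monitors participants. The 10% missing data refers to the post-treatment primary outcome, not to one-year costs. The abstract says only that cost-effectiveness will be explored.

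**Conclusion.** The point holds in a limited form. The ICER is a poor choice of estimate where the effect difference is expected near zero. The sign result rests only on a zero true QALY difference and a clear cost saving, not on any assumed QALY SD. The dollar ranges do rest on assumed inputs and show order of magnitude only.

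The societal cost sentence is a caution about interpretation, not a faulty decision rule. Under the assumed SD of USD 5,000 and 78 per arm, true differences several times the assumed saving of 180 would usually be non-significant (76% of trials at 1,000), while about 2,240 would be detected with 80% power. The primary non-inferiority conclusion is untouched. This is a cheap improvement to one secondary hypothesis.

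**What to change.** Use the 5,000 paired bootstrap samples already planned.

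1. Base secondary hypothesis 2 on incremental net monetary benefit with a 95% confidence interval over a stated range of willingness-to-pay values, and show the acceptability curve.
2. Adjust QALYs for baseline EQ-5D, which the measurement table already collects.
3. Report the ICER only as a descriptive figure, with its quadrant.
4. Report the societal cost difference with its confidence interval, and state that a non-significant result will not be taken as equality.

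No new data, visits or staff are needed. The cost is a little extra analysis and the need to fix a threshold range before the data are seen. The authors should also expect that the net benefit interval may include zero over much of that range (step 4 of the working).
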